#### Analysis of primary outcome

Change in peak length of the RF and TS muscles during gait at 1 month (difference in length between V3 and V1 will be compared between groups using a Student t-test. To prevent the risk of false positives induced by multiple testing, a Bonferroni Holm correction will be applied to the *p*-values for peak length, peak force and peak strength [61]. The level of significance will be set at 0.05/3.

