### Clinical evaluation

All patients will undergo a comprehensive clinical evaluation. To limit inter-investigator variability, one physiotherapist in each centre will carry out all assessments. In addition, this physiotherapist will be blinded to group allocation.The clinical examination will include passive range of motion (ROM) of the hip, knee and ankle using a manual goniometer. Measurement of joint ROM will be carried out according to the protocol recommended by Clarkson [22]. Spasticity will be evaluated using the Modified Ashworth Scale (MAS) [23]. This scale has been validated for the evaluation of spasticity [24, 25] and is sensitive to change following BTX-A treatment [26]. Lastly, strength of the hip extensor, flexor and abductor, knee flexor and extensor, ankle dorsiflexor and plantarflexor muscles of the affected and non-affected lower limbs will be measured using the Medical Research Council (MRC) scale [27, 28] (Table 2).

**Table 2 Tab2:** Summary of outcome measures for each study aim

Aims	Parameter evaluated	Outcome measure
First	Peak length of RF and TS during gait	3D analysis
		MSM
	Peak strength of RF and TS	Isometric evaluation
Second	Inter-segmental gait coordination	3D analysis:
		EMG analysis
		Muscle synergies
		Peak joint angles
		Peak joint torques
		Inter joint coordination
		ABILOCO scale
		TUG
		6MWT
		10MWT
		Stairs test
	Balance	Berg balance scale
		ABC scale
Third	Independence	FIM
	Quality of life	SF 36

*RF* rectus femoris, *TS* triceps surae, *TUG* Timed up and go test, *6MWT* Six minute walk test, *10 MWT* Ten meter walk test, *ABC scale* Activities Balance Confidence scale, *FIM* Functional independence measure, *SF 36* Short form (36) health survey, *3D analysis* gait motion analysis, *MSM* Musculoskeletal models

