## Outcome measures

### Primary aim: Outcome

The primary outcome is change in maximal length of the injected muscles during gait one month after injection of BTX-A or placebo, quantified by 3D motion analysis and a musculo-skeletal model. It will be determined by comparison of the results of the evaluations carried out at V1, V3 and V4.

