#### Inter-segmental coordination during locomotion

Inter segmental coordination during gait will be analyzed using a 3-dimensional (3D) motion capture system (Motion Analysis Corporation, Santa Rosa, CA, USA, six cameras, Sampling Frequency 100 Hz) and two force plates (AMTI, Watertown, MA, USA, Sampling Frequency 1000 Hz). The trajectories of 24 markers placed on anatomical landmarks using the Helen Hayes marker set will be recorded and filtered using a fourth-order zero-lag Butter worth low-pass-filter with a 6 Hz cut off frequency.

3D Gait Analysis will be carried out during V1, V3 and V4. To limit inter-investigator variability, one operator in each centre will carry out all assessments. In addition, this operator will be in blinded to group allocation. Two conditions will be analysed: preferred and maximal walking speed. For each condition, eight trials will be recorded to ensure a minimum of ten gait cycles from both lower limbs. Boudarham et al. suggested that during 3D analysis, there is a phase of adaptation during which gait is unstable [42]. They thus suggested kinematic and kinetic analysis should be based on three to nine gait trials in patients with hemiparesis.

OrthoTrack 6.5 software (Motion Analysis Corporation, Santa Rosa, CA, USA) will be used to calculate kinematic and kinetic parameters, using Euler rotations (Grood and Suntay method) for the kinematic parameters.

Spatio-temporal parameters will be calculated for both lower limbs, including gait velocity, cadence, step and stride length, step width, and the duration of the single support phase. Kinematic and kinetic parameters will be calculated for both lower limbs for each sub-phase of the gait cycle (initial double contact phase, single support phase, final double contact phase and swing phase). The main kinematic parameters are peak flexion, extension, peak abduction, adduction, valgus/varus and rotation as appropriate for the pelvis, hips, knees and ankles. Ground reaction force and peak joint moments of the hips, knees and ankles will be calculated in the three dimensions of space.

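### The 0.05/3 level counts three measures, but each is defined on two muscles with no combining rule, so 5% family-wise control is not assured

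*Protocol article*

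**What the plan says.** Under Analysis of primary outcome, the change from V1 to V3 is compared between groups by Student t-test for "Change in peak length of the RF and TS muscles during gait at 1 month". The purpose of the correction is given as "To prevent the risk of false positives induced by multiple testing". The method is that a "Bonferroni Holm correction will be applied to the *p*-values for peak length, peak force and peak strength", and the next sentence reads "The level of significance will be set at 0.05/3".

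Both muscles appear for every measure:
- **Length:** under Primary aim: Outcome, "The primary outcome is change in maximal length of the injected muscles during gait one month after injection of BTX-A or placebo". Table 2 (in Clinical evaluation) lists "Peak length of RF and TS during gait".
- **Force:** the secondary aims at the end of the Background name RF and TS.
- **Strength:** Table 2 names RF and TS. The Maximal strength section, however, describes knee testing only (quadriceps and hamstrings for the isometric test), with no ankle test.

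The section on inter-segmental coordination says of the gait analysis: "Two conditions will be analysed: preferred and maximal walking speed". No section says which condition supplies the primary peak length. Primary aim: Outcome adds, of the one-month outcome, "It will be determined by comparison of the results of the evaluations carried out at V1, V3 and V4".

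**The concern.** A divisor of three protects 5% only if each measure yields one decision. With two muscles per measure and no rule for joining them, the plan does not define what result counts as positive. If either muscle may carry a measure, more tests are made than the divisor allows for. If both must succeed, the error is protected but the trial is smaller than its power statement implies, because the sample size used an unadjusted 5% and a pilot study of RF alone. Left open until the data are unblinded, the choice of rule could turn the same data into a positive or a negative result. The level and the method also disagree: Holm is a sequence of thresholds, not one fixed level.

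**Working it through.** **Inputs.** Level 0.05/3 and the three measures: Analysis of primary outcome. Two muscles: Background aims, Table 2, Primary aim: Outcome. Two speeds: Inter-segmental coordination during locomotion. Two-sided 5%, 80% power, 17 per group, 40 in total: Sample size calculation.

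**1. The plan's own figure.** Bonferroni with m = 3 gives 0.05/3 = 0.0167. For three independent tests, 1 − (1 − 0.0167)^3 = 4.9%, with an upper bound of 3 × 0.0167 = 5.0%. The divisor is right for three tests.

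**2. Counting the tests, one speed.** Three measures × two muscles = 6. Because no TS strength test is described, the count as measured is 2 (length) + 2 (force) + 1 (knee extensor strength, standing for RF) = 5.

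**3. Error if each muscle is tested separately at 0.05/3** (independent tests: 1 − (1 − 0.05/3)^m; bound: m × 0.05/3).

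| Tests | Independent | Bound |
|---|---|---|
| 3 (as counted by the plan) | 4.9% | 5.0% |
| 5 | 8.1% | 8.3% |
| 6 | 9.6% | 10.0% |
| Length only, 2 muscles, 1 speed | 3.3% | 3.3% |
| Length only, 2 muscles, 2 speeds | 6.5% | 6.7% |

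When no effect exists anywhere, only the first Holm step matters, so these figures also apply to Holm started at 0.05/3.

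**4. Correlation, six tests** (200,000 simulated trials; the correlations are assumptions, as the protocol gives none).

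| Within a measure | Between measures | Error |
|---|---|---|
| 0.5 | 0 | 9.2% |
| 0.8 | 0 | 7.8% |
| 0.8 | 0.5 | 6.9% |
| 0.9 | 0.8 | 4.9% |

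Only the extreme last case returns to 5%.

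**5. If both muscles must be significant.** Each measure's error is at most 0.0167, so the family is at most 3 × 0.0167 = 5%. The cost is power. The protocol states no effect size; 17 per group at two-sided 5% and 80% power back-solves to a standardised difference of about 0.99 (an assumption). At 0.05/3 one test then has 64% power with 17 per group and 73% with 20. Two muscles together cannot exceed these figures. If TS had the same effect and were independent of RF, joint power would be 0.643² = 41% and 0.733² = 54%; positive correlation would raise both. Later Holm steps, when reached, would also help.

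**6. Level against method.** Holm on three p-values compares them in order with 0.05/3, 0.05/2 and 0.05. One fixed 0.05/3 is plain Bonferroni. Comparing Holm-adjusted p-values with 0.05/3 would correct twice, with a first step of 0.05/9 = 0.0056.

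**The case against.** The strongest reply is that the excess depends on a reading the protocol does not state. Family-wise error is at most 5% if both muscles are required, if one value per measure is used, or if Holm runs over every muscle-level p-value (though that last reading does not fit 0.05/3). Even the literal double correction would hold it: 6 × 0.05/9 = 3.3%. Moreover, the primary outcome is length, and RF and TS lengths at one speed stay at 3.3%. The excess arises over the declared three-measure family, two of whose members the protocol lists as secondary outcomes. All of this stands, and it is why the conclusion is that control is not assured. A reader might infer that 5% is definitely breached; the text does not support that.

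Two further inferences also fail. One is that each measure is tested at two speeds, giving twelve tests and about 18% error. Strength is a seated dynamometer test, so speed can apply only to length and force, and the protocol leaves the primary speed open rather than saying both are tested. The other is that V4 adds a primary test. Analysis of primary outcome uses V3 minus V1, and Analysis of secondary outcomes places the three-month comparison among the secondary ones. The mention of V4 under the primary outcome is loose wording that needs aligning.

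It may also be said that such detail belongs in a statistical analysis plan. That would excuse silence, but here the protocol states a divisor, and it does not match the muscles that the protocol itself lists.

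**Conclusion.** The point stands in this form: the stated level counts three hypotheses, the protocol's definitions yield five or six at a single speed, and no rule reconciles them. With separate muscle tests at 0.05/3, error over the declared family is 8.1% to 9.6% under independence, and about 7% to 9% for six tests under plausible correlation. For length alone the level is adequate at one speed (3.3%) but not at both (6.5%). With both muscles required, error is held and the shortfall moves to power. The size of that shortfall is less certain: 64% and 73% per test rest on a back-solved effect, and the joint figures also assume an equal TS effect and independence, which an RF-only pilot cannot support. The conflict between a fixed 0.05/3 and Holm needs no assumption.

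**What to change.** Before unblinding, amend the protocol or analysis plan as follows.

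1. Name one walking speed for peak length and peak force; treat the other as secondary.
2. State whether a measure succeeds on RF, on TS, or only on both.
3. Choose one correction that fits that rule:
   - **Separate muscles:** apply Holm to every RF and TS p-value actually tested, with steps 0.05/m, 0.05/(m − 1), …, 0.05. Here m = 6 if a TS strength test is specified and m = 5 if it is not.
   - **Both muscles:** require RF and TS for each measure and apply Holm across the three measures (0.05/3, 0.05/2, 0.05). Say what strength rests on if no TS test exists.
4. Delete the sentence fixing the level at 0.05/3.
5. Remove V4 from the description of the one-month primary outcome, so that it agrees with the two analysis sections.

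A fixed sequence starting with RF is also acceptable but not required; it would put one muscle ahead of an aim that names both.

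The cost is wording only, with no new data or visits. The statistical price should be stated. Separate testing has a first threshold of 0.05/6 = 0.0083 or 0.05/5 = 0.01 instead of 0.0167; at 0.0083 and the back-solved effect, first-step power per test is 54% with 17 per group and 64% with 20. Requiring both muscles gives the lower joint power shown in the working.

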### Randomization method

All patients included are routinely followed in the spasticity-units of the three participating centers. All will already be treated with BTX-A and will have undergone regular spasticity ratings using the MAS. Patients with spasticity of both the RF and TS will therefore be identified before the study is presented to them during visit 1. In addition, all patients will already have undergone routine 3D gait analysis as part of their management, thus the decrease in peak knee flexion and peak ankle plantarflexion in swing phase will already be documented, with the cause reported as RF and TS spasticity. Randomization will be carried out using randoWeb software (http://randoweb.aphp.fr) at the beginning of visit 2, then either BTX-A or the placebo will be injected according to group allocation. To avoid problems relating to expiration of the BTX-A, the BTX-A and placebo packs will be randomized, not the patients. A randomization list will be uploaded on a dedicated server (CleanWeb) and each patient will be attributed an injection pack number. The randomization will be block-balanced. Patients will thus be injected with either BTX-A or the placebo at visit 2.

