## Statistical analysis

### Sample size calculation

Sample size was estimated using G*power software [59]. The input data were taken from Lampire et al. [15] who assessed the effect of BTX-A injection on length and lengthening velocity of rectus femoris during gait in chronic stroke patients). Using a two-tailed test at a threshold of 5% and a power of 80%, a sample of seventeen subjects per group was found to be necessary [60]. We therefore plan to recruit forty patients to take into account potential patients lost to follow-up. The study is currently underway. On the first of April 2018, twenty-eight participants had been included.

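### The unadjusted t-test on change in peak length is valid but leaves the V1 measurement's precision unused; a prespecified ANCOVA on baseline would use it for one degree of freedom

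*Protocol article*

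**What the plan says.** The section on the analysis of the primary outcome names the method outright: the "difference in length between V3 and V1 will be compared between groups using a Student t-test". It lists no covariate. The same section applies a Bonferroni-Holm correction over peak length, peak force and peak strength, and adds: "The level of significance will be set at 0.05/3". The section on secondary outcomes uses the same test for the three-month visit (V4).

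Table 1 and its footnote show that every outcome is measured at V1, V3 and V4, so each patient should have a baseline peak length.

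The sample size section works at a two-sided level of 5% with 80% power and concludes that "a sample of seventeen subjects per group was found to be necessary". To cover losses, the target is then raised: "We therefore plan to recruit forty patients to take into account potential patients lost to follow-up". The inputs come from a pilot study "who assessed the effect of BTX-A injection on length and lengthening velocity of rectus femoris during gait in chronic stroke patients". No effect size, standard deviation or V1–V3 correlation is reported.

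On centres, there are three. For gait analysis, "one operator in each centre will carry out all assessments". On allocation: "The randomization will be block-balanced". Stratification by centre is not stated.

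**The concern.** A change-score test subtracts the whole baseline value, so it assumes that a patient who starts 1 mm above average is expected to finish 1 mm above average. When two measurements are imperfectly correlated and have similar spread, the expected carry-over is less than 1 mm. The change score then carries part of the baseline noise into the treatment comparison. It also over-corrects when the arms happen to differ at baseline, which is a real possibility with about 20 patients per arm.

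The stake is precision, not validity. The trial is small, and its primary comparison is to be tested at a stricter level than the one used to size it. Precision from a value already collected is therefore worth having.

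**Working it through.** **Inputs.** From the protocol: 17 per group, two-sided 5%, 80% power, 40 recruited, test level 0.05/3 = 0.0167. Assumed: 1:1 allocation (20 per arm), equal variances at V1 and V3, and a V1–V3 correlation ρ of 0.5 to 0.9.

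**1. The plan's own figure.** No effect size is given, so 17 per group can only be back-solved. With the two-sample noncentral t (noncentrality d·√(n/2), 2n − 2 df), d = 0.991 SD of change gives exactly 80% at n = 17 and a level of 0.05. I use this d throughout.

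**2. Planned t-test at both levels.**

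| per arm | noncentrality | power at 0.05 | power at 0.05/3 |
|---|---|---|---|
| 17 | 0.991·√8.5 = 2.889 | 80.0% | 64.3% |
| 20 | 0.991·√10 = 3.134 | 86.3% | 73.3% |

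**3. Variance ratio.** With a common variance σ², the change score has variance 2σ²(1 − ρ). The ANCOVA residual variance is σ²(1 − ρ²). The ratio is (1 − ρ²) / [2(1 − ρ)] = (1 + ρ)/2, that is 0.75, 0.85, 0.90 and 0.95 for ρ = 0.5, 0.7, 0.8 and 0.9.

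**4. Cost of estimating the slope.** One degree of freedom is lost (2n − 3). Chance baseline imbalance inflates the variance on average by 1 + 1/(N − 4), with N = 2n: 1 + 1/30 = 1.033 at n = 17 and 1 + 1/36 = 1.028 at n = 20.

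**5. Power of baseline ANCOVA at 0.05/3.** The noncentrality is d·√(n/2) / √[ratio × inflation]. For n = 20 and ρ = 0.7 this is 3.134 / √(0.85 × 1.028) = 3.35, which gives 79.6%.

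| per arm | t-test | ρ = 0.5 | ρ = 0.7 | ρ = 0.8 | ρ = 0.9 |
|---|---|---|---|---|---|
| 20 | 73.3% | 85.0% | 79.6% | 77.0% | 74.3% |
| 17 | 64.3% | 76.9% | 70.7% | 67.8% | 65.1% |

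Simulation with 8,000 runs per setting agreed to within about 1 point.

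**6. Where the gain ends.** At 20 per arm ANCOVA and the t-test break even at ρ of about 0.94. At ρ = 0.95 ANCOVA has 73.1% against 73.3%, so the possible loss there is negligible.

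**7. Adding centre, with no centre effect on change.** Two more degrees of freedom (2n − 5) and inflation 1 + 3/(N − 6):

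| per arm | ρ = 0.5 | ρ = 0.7 | ρ = 0.8 | ρ = 0.9 |
|---|---|---|---|---|
| 20 | 82.4% | 76.7% | 74.0% | 71.3% |
| 17 | 73.2% | 66.9% | 63.9% | 61.2% |

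Against baseline alone this costs about 3 points at 20 per arm and about 4 at 17. At ρ = 0.9 the result is below the t-test at both sizes; at 17 per arm this is already so at ρ = 0.8.

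**8. Chance imbalance.** At 20 per arm the baseline difference has a standard error of √(2/20) = 0.316 SD. It shifts the change-score estimate by (1 − ρ) × 0.316, that is 0.16, 0.09 and 0.03 SD at ρ = 0.5, 0.7 and 0.9. In the same units the assumed effect is 0.991·√[2(1 − ρ)] = 0.99, 0.77 and 0.44 SD, so the shift is about 16%, 12% and 7% of it. The variance in step 3 already includes this; it is not an additional loss.

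**The case against.** The strongest reply is that nothing here is wrong. A t-test on change is unbiased over randomisation, holds its type I error and matches a primary outcome declared as a change. That stands. A reader might infer that the planned test is biased, but the over-correction applies only conditional on an observed imbalance.

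A reader might also infer that adjustment would restore most of the power lost by testing at 0.05/3. The document does not support that, because it gives no correlation. At 20 per arm the loss is 86.3 − 73.3 = 13.0 points, and baseline adjustment recovers about 90% of it at ρ = 0.5, 49% at 0.7, 28% at 0.8 and 8% at 0.9. A high correlation is plausible: length is normalised within patient, at least ten gait cycles are planned, and one operator per centre does all assessments. A lower one is plausible too, since the protocol claims only that normalisation reduces marker-placement differences between visits. The loss is itself an upper bound: under Holm, 0.05/3 applies only to the smallest p-value. Sizing at 5% while testing at 0.05/3 is a separate matter that ANCOVA does not settle.

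A third tempting step is to adjust for centre because each centre has its own operator. The protocol points the other way: with the same operator at every visit, a constant centre offset cancels in V3 − V1. Centre helps only if the change itself differs between centres, and nothing in the document suggests that. No stratification by centre is stated that would call for it.

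Finally, repeated-measures models for peak length are already planned. They are secondary, however, and do not alter the primary test.

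**Conclusion.** The point holds as a precision improvement, not as the correction of an error. The protocol fixes an unadjusted change-score test although a baseline value is available. Over the assumed correlations of 0.5 to 0.9, baseline ANCOVA has higher power than the t-test at both 17 and 20 per arm. The gain at 20 per arm runs from about 12 points at ρ = 0.5 to about 1 point at ρ = 0.9.

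These figures rest on 1:1 allocation, equal V1 and V3 variances, an effect back-solved from 17 per group, a correlation that is assumed throughout, and a flat 0.05/3 as the worst case under Holm. The direction of the recommendation is secure short of a correlation of about 0.94 at 20 per arm. The size of the benefit is not known.

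**What to change.** Replace the primary t-test with a prespecified ANCOVA of V3 peak length on treatment and V1 peak length. The treatment coefficient is the same whether V3 or V3 − V1 is the response, so the target remains the difference between arms in one-month change. Use the same model at V4 and for peak force and peak strength, each with its own baseline. Report the adjusted difference with a 95% confidence interval, and keep the t-test as a sensitivity analysis. Leave centre out of the primary model; it can be examined as a sensitivity analysis.

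The cost is one degree of freedom and a protocol amendment, for which the section on changes to the planned analysis provides a route. No new data are needed. The article reports 28 patients included on 1 April 2018 with patients, injectors and evaluators blinded, so the change should be fixed and dated before unblinding.

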Muscle force generated during gait has never been evaluated using a musculoskeletal model after BTX-A injection. Because BTX-A injection blocks transmission at the neuromuscular junction and is known to reduce muscle force evaluated by static tests, we believe it is important to evaluate the effect of BTX-A on force generated during gait. We hypothesise that force produced by the RF and TS muscles during gait will be decreased following BTX-A injection but not after the placebo injection.

The main aim of this randomised, placebo-controlled, triple blind study is to evaluate the effect of BTX-A injection in the RF and TS muscles on their peak length during gait in patients with chronic stroke.

The secondary aims are to: i) evaluate peak force generated by the RF and TS during gait following BTX-A injection, ii) evaluate changes in inter-segmental coordination during gait following BTX-A injection, iii) evaluate the impact of BTX-A injection on quality of life and iv) compare the effect of BTX-A injection with a placebo injection on the parameters specified above, in patients with chronic stroke.

The third aims are to: i) evaluate the quality of life, ii) evaluate the functional independence in motor and cognitive domains, iii) evaluate the locomotor ability.

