### Secondary aim: Outcomes

The secondary outcomes are peak muscle force generated during gait assessed by the MSM, peak force measured during the isometric evaluation, inter-segmental coordination during gait assessed by 3D analysis, and functional tests.

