#### Analysis of secondary outcomes

The statistical test used for the primary outcome will also be used to evaluate the effect of BTX-A at 3 months (V4). To compare changes in the secondary criteria across visits between the two groups (change in peak length of injected muscles, joint angles, modified Ashworth score, functional scores and quality of life), repeated measures models will be used. Depending on the distribution of continuous or binary variables, mixed models or generalized estimation equations (GEE) will be used respectively. The models will include the treatment variable (BTX-A or placebo), time and interaction between time and treatment as explanatory factors. If a significant interaction is found, comparisons between both groups (BTX-A and placebo) will be carried out for each time-point using a Student t-test. In order to take in to account any effects of multiple testing, these outcomes will be considered as explanatory factors rather than determinants of the effectiveness of BTX-A.

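### Peak length is the only primary outcome in the aims, but the primary analysis puts it in one unordered Holm family with two secondary outcomes and never says which result decides the trial

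*Protocol article*

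**What the plan says.** Three places in the protocol article rank peak length alone as primary.

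- *Background* gives the main aim as to "evaluate the effect of BTX-A injection in the RF and TS muscles on their peak length during gait". The first secondary aim is to "evaluate peak force generated by the RF and TS during gait following BTX-A injection".
- *Primary aim: Outcome*: "The primary outcome is change in maximal length of the injected muscles during gait one month after injection of BTX-A or placebo".
- *Secondary aim: Outcomes*: "The secondary outcomes are peak muscle force generated during gait assessed by the MSM, peak force measured during the isometric evaluation", followed by coordination and functional tests.

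Two places rank the measures differently.

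- *Analysis of primary outcome* compares the 1-month change in length of RF and TS by t-test, then applies one Bonferroni-Holm correction to the p-values "for peak length, peak force and peak strength", with significance set at 0.05/3. No order among the three is given.
- Table 2 (in *Clinical evaluation*) lists "Peak strength of RF and TS", measured isometrically, in the row for the first aim beside peak length. Modelled peak force during gait has no row.

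*Sample size calculation* uses a two-sided 5% level and 80% power, and arrives at 17 per group with 40 to be recruited.

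**The concern.** The article does not settle which result decides the trial. If *Primary aim: Outcome* governs, a trial with no significant length difference is negative, whatever happens to force and strength. If the Holm family under the primary heading governs, force or strength can be rejected on its own, and that rejection sits under the primary analysis. The same data could then be reported in two ways.

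This matters because the measures are not interchangeable. The question asked is whether the muscles lengthen during gait. A loss of static strength is an expected drug effect: *Background* says the toxin "is known to reduce muscle force evaluated by static tests". A strength result alone would not answer the main question.

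There is also a cost in power. The trial was sized for one test at 5%, but length is now first tested at 0.05/3.

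**Working it through.** **Inputs from the article:** 17 per group, 40 recruited (20 per group), two-sided 5%, 80% power, three endpoints, level 0.05/3 = 0.0167.

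**Assumptions:** no effect size or SD is given, so the standardised effect d must be assumed. I take peak strength to be the isometric measure, as Table 2 does, and count each of length, force and strength as one test.

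**1. The planned sample size.** Without an effect size, 17 per group can be neither confirmed nor refuted, only back-solved. For a two-sample t-test with n per group, df = 2n − 2 and noncentrality d√(n/2). Solving power = 0.80 at n = 17 and two-sided 0.05 gives d = 0.991, that is, noncentrality 0.991 × √8.5 = 2.89. The normal approximation (1.960 + 0.842) × √(2/17) gives 0.961.

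**2. Power for length at the two levels, d = 0.991.**

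| n per group | at 0.05 | at 0.05/3 |
|---|---|---|
| 17 | 80% | 64% |
| 20 | 86% | 73% |

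Restoring 80% at 0.05/3 needs about 22-23 per group. Holm tests the second and third smallest p-values at 0.025 and 0.05, so the loss shrinks if force or strength is rejected first.

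**3. Chance of at least one rejection when length truly does not change.** Holm rejects something whenever the smallest of the three p-values is at or below 0.0167. With independent measures, the chance is 1 minus the product of the three chances of not rejecting. At 17 per group, single-test power at 0.05/3 is 0.159 for d = 0.5 and 0.643 for d = 0.991.

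- Strength only, d = 0.5: 1 − 0.983 × 0.983 × 0.841 = 0.19
- Force and strength, d = 0.5: 1 − 0.983 × 0.841² = 0.30
- Force and strength, d = 0.991: 1 − 0.983 × 0.357² = 0.87

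Simulation with correlation between measures from 0 to 0.8 gives these ranges at 17 per group:

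| True effects (length = 0) | At least one p ≤ 0.05/3 |
|---|---|
| Strength only, d = 0.5 | 17-19% |
| Force and strength, d = 0.5 | 23-30% |
| Force and strength, d = 0.8 | 55-69% |
| Strength only, d = 0.99 | about 65% |
| Force and strength, d = 0.99 | 75-88% |

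Nearly all of this is force or strength rejected without length. At correlation 0.5 to 0, that event alone has probability 25-28% for d = 0.5 and 77-84% for d = 0.99. The assumed effect matters far more than the correlation.

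**4. Error control.** With no effect on any measure, the chance of any rejection is 4.4-5.0% (correlation 0.5 to 0). The family-wise error is controlled, so the fault is an undefined decision and not alpha inflation.

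**5. The two muscles.** Peak length covers RF and TS. If each is tested at 0.05 and either counts, the error for length alone is 1 − 0.95² = 9.75% when independent, and about 8% at correlation 0.8. Testing length first at 0.05 therefore holds 5% only with a rule for the two muscles.

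**The case against.** The strongest reply is that *Primary aim: Outcome* controls, and that Holm only protects two further claims. Holm supports endpoint-specific statements: rejecting the force null supports a claim about force and nothing more. The closing paragraph of *Management of changes to the planned analysis* also lists length, force, coordination and function as separate questions. This reading is open, but nothing in the article fixes it. The primary heading over the family and the first-aim row of Table 2 pull the other way.

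Three stronger inferences are tempting, and the text does not support them.

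- **That the trial will be declared positive on weakening alone.** No section states that one significant result of three is enough. The article leaves this possible but does not plan it.
- **That *Analysis of secondary outcomes* makes all three measures decisive.** It says "these outcomes will be considered as explanatory factors rather than determinants of the effectiveness of BTX-A" and does not name force or strength among its criteria. But its list includes peak length itself, so it does not separate primary from secondary measures. The disclaimer can equally be read as covering the force measures.
- **That a fall in force is already known.** The remark in *Background* concerns static tests. The same paragraph says that force during gait has not been modelled after the toxin, so the argument reaches strength only.

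The 75-88% figure also moves an effect size back-solved from a length-based sample size onto force and strength, which nothing in the article supports. It is the upper end of a range.

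**Conclusion.** The contradiction is in the text. Length alone is primary in the aims and outcome sections, while the primary analysis and Table 2 place force, strength or both beside it. Because no order and no success rule are given, a force or strength rejection could be presented as a primary result.

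How likely this is when length does not change runs from about 17% to 88% at 17 per group, depending wholly on assumed effects of d = 0.5 to 0.99 and on whether one or both measures fall. The power cost is firmer, but it too rests on the back-solved d: 64% against 80% at 17 per group and 73% against 86% at 20, before any relief from Holm's later steps. This should be corrected. It does not show inflated error or an adopted any-one-wins rule.

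**What to change.** In *Analysis of primary outcome*, name the 1-month between-group difference in peak length as the sole primary outcome, tested first at a total two-sided 0.05, with an explicit rule for RF and TS. Two workable rules are:

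- both muscles significant at 0.05. This holds the error but lowers power: with d = 0.991 in each and independent measures, 0.80 × 0.80 = 64% at 17 per group, rising towards 80% as the correlation approaches 1;
- Holm across the two muscles.

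Restate the power in *Sample size calculation* for the rule chosen. Test peak force and peak strength only after the length step succeeds, in fixed sequence or by Holm within the pair, and state that they cannot establish effectiveness on their own. Move peak strength out of the first-aim row of Table 2, and make *Analysis of secondary outcomes* say where the two force measures belong.

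Keeping the three-way family and merely stating that length decides would settle the labels. It would leave length starting at 0.05/3, so the trial would need re-powering.

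The cost is wording, with no new data. No confirmatory claim on force or strength is possible if length is not significant, which fits their secondary status. *Management of changes to the planned analysis* requires committee validation and a justified amendment. With 28 of 40 patients included on 1 April 2018, this should be documented before unblinding.
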